**Methods:**

Volunteer participants will be recruited via social media and posters at the university. They will be randomly assigned to an experimental group or a waiting list control group. Both groups will complete two assessment sessions (before and after the intervention) consisting of questionnaires measuring cognitive and emotional variables as well as experimental tasks measuring cognitive biases (i.e. attention, memory, and interpretation). After the first assessment session, only participants in the experimental group will receive a link to follow the four CBM-I_Clin_ sessions at home. All participants will receive, via email, follow-up questionnaires 2 weeks and 3 months after the second assessment.

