It is hypothesised that there will be a significant change in interpretation bias (less negative or more positive/neutral) from pre-intervention to post-intervention in the experimental group in comparison to the control group. It is also expected that changes in interpretation biases will also be associated with significant changes in attention and memory biases (less negative or more positive/neutral) from pre-intervention to post-intervention in the experimental group in comparison to the control group. Finally, it is hypothesised that the intervention will help the experimental group to reduce symptoms of depression and anxiety and increase well-being from pre-intervention to post-intervention in comparison to the control group. Due to the lack of conclusive findings from previous studies, it is explored whether these changes are maintained over time (after 2 weeks and 3 months) and the temporal dynamics of the different cognitive bias processes (attention, interpretation, and memory).

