### Sample size

The sample size was calculated based on the estimated effect size of the change in interpretation bias before and after a CBM-I intervention (*d* = .43) according to a recent meta-analysis on the field [20]. Following G*Power calculations [39], the minimum sample size (*α* set at 0.05, power at 0.95) to find a difference in a repeated-measures multivariate analysis of variance with one within-subjects factor (two-time points) and one between-subjects factor (two groups) was 73 participants. Due to expected attrition [40], 20% more participants will be recruited, reaching a total sample size of 88 participants.

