**Fig. 4 Fig4:**
[figure not shown]
Schedule of enrolment, interventions, and assessments

After completion of the three lab tasks, participants in the experimental group will receive in their email the link to complete the online programme from home. They will need to log in to an online platform created for this study and will be invited to create their own account and password to access the materials. Information will be stored solely using the participant’s code number and only the main researchers will have access to the data. These data will be recorded in the database of the platform and will be used by the researchers to monitor if participants in the experimental group complete all four online sessions before the post-intervention evaluation. When participants first access the platform, they will find only the first session available. Access to the next session will be granted only 24 h after completing the previous one. This intermission between sessions aims to enhance participants’ processing of the contents of each session as well as to avoid cognitive overload and boredom.

After finishing the 4-session training programme, participants in the experimental group will be notified again, after approximately 10 days, for a second assessment session. The control group will be allowed to complete the intervention right after the second assessment. To improve adherence, both groups will receive a reminder for the second assessment session the day before. Finally, participants will be sent the follow-up questionnaires (AST-D-II, DASS-21, PHI, SE) twice (in the next 2 weeks and 3 months). To increase adherence during the follow-ups, participants will be sent up to a maximum of three reminders to complete questionnaires. Both groups will have the opportunity to complete a ‘feedback question’ to give their opinion about the intervention. This question will be included in the post-assessment for the experimental group and at the follow-ups for the control group.

The procedure has been approved by the university ethics committee (Ref. 2018/19-017) and has been registered (ClinicalTrials.gov NCT03987477). Moreover, it follows the recommendations for a clinical trial protocol [70].

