### Analytic plan

Demographic data and pre-treatment measures will be analysed to test for group differences with analysis of variance and chi-squared test for nominal variables.

Complete case analyses will be conducted for those participants who complete all 4 online sessions and attend pre- and post-assessment evaluation sessions. A series of 2 (group: experimental, control) × 3 (symptom group: never, present, past) × 2 (time: pre-training, post-training) analyses of variance will be performed to evaluate the change between groups. The symptom group will be created based on present and past symptoms of depression and/or anxiety to explore their influence on the results. Intention-to-treat (ITT) analyses will be conducted with all participants, regardless of session or outcome measure completion. ITT mixed models (restricted maximum likelihood (REML) estimation) will be used to account for missing data [71]. Binary logistic regression will be used to evaluate the assumption that data is Missing at Random (MAR). Exploratory mediation analyses will be conducted to study the interplay between the different cognitive bias scores given the change of the intervention. Finally, follow-up assessments will be included in a series of analyses of variance to evaluate group differences in time. All analyses will be performed in SPSS Statistics 20 with an *α* level of 0.05.

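### Controls may take the programme before both follow-ups, so later group differences compare immediate with delayed access, and a narrowing gap cannot be read as lost benefit

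*Protocol article*

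**What the plan says.** Four statements in the protocol article bear on this point.

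- **Control access** (Procedure): "The control group will be allowed to complete the intervention right after the second assessment".
- **Follow-up timing** (Abstract, Methods): "All participants will receive, via email, follow-up questionnaires 2 weeks and 3 months after the second assessment". The Procedure lists AST-D-II, DASS-21, PHI and the stressful-events questionnaire as the instruments.
- **Follow-up analysis** (Analytic plan): "follow-up assessments will be included in a series of analyses of variance to evaluate group differences in time".
- **Purpose** (Objectives and hypotheses): for lack of conclusive earlier findings, "it is explored whether these changes are maintained over time (after 2 weeks and 3 months"). The changes meant are those of the experimental group relative to the control group from pre- to post-intervention.

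No section holds back control access until the follow-ups are complete, and none says how controls who have taken the programme are to be treated in the follow-up comparison.

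**The concern.** The waiting list ends at the second assessment, and both follow-ups are counted from that same assessment. Up to that point the randomised contrast is programme versus no programme. After it, the contrast is earlier versus later access.

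The follow-up question is whether the benefit lasts, yet the one follow-up analysis the article states compares the groups. If controls take the programme and improve, the arms move together even when the experimental arm has lost nothing. A reader of the group comparison alone could then report that the benefit faded when it had not.

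**Working it through.** **1. Can controls finish before the follow-ups?** The Procedure states that "Access to the next session will be granted only 24 h after completing the previous one". Four sessions have three gaps, so the shortest course takes about 3 × 24 h = 72 h, or 3 days, against 14 days to the first follow-up. On the question asking for an opinion of the intervention, the Procedure adds: "This question will be included in the post-assessment for the experimental group and at the follow-ups for the control group". The plan thus appears to expect that at least some controls will have used the programme by then. It gives no figure for how many.

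**2. What the follow-up contrast measures.** Write, in SD units:
- d: the programme effect at post-test;
- δ: the part of it lost by the experimental arm by follow-up;
- p: the share of controls who have completed the programme by follow-up;
- b: the average benefit those controls show at that time.

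The expected group difference at follow-up is D = (d − δ) − p·b. With full maintenance (δ = 0) and equal benefit (b = d), this becomes D = (1 − p)d.

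**3. The plan's own figure.** The Sample size section takes d = 0.43, α = 0.05 and power 0.95 for two groups and two time points, and reports 73 participants. Using the G*Power within-between interaction, with f = d/2 = 0.215, m = 2 time points, an assumed correlation ρ = 0.5 (not stated in the article) and λ = f²·N·m/(1 − ρ):
- λ at N = 73 is 0.215² × 73 × 2/0.5 = 13.50;
- power is 0.952 at N = 73 and 0.949 at N = 72, so 73 is reproduced.

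This calculation covers pre and post only. It is used below as a yardstick.

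**4. Dilution with full maintenance.** The inputs are d = 0.43, N = 73 and the convention of step 3; p is assumed and shown across its range.

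| p | D = (1 − p) × 0.43 | Power |
|---|---|---|
| 0 | 0.43 | 0.95 |
| 0.25 | 0.32 | 0.78 |
| 0.50 | 0.215 | 0.44 |
| 0.75 | 0.11 | 0.15 |
| 0.90 | 0.04 | 0.07 |
| 1 | 0 | 0.05 (the α level) |

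A plain comparison of two means with 36.5 per arm starts lower, at power 0.45 for p = 0, and falls to 0.15 at p = 0.5. The direction is the same.

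**5. Two histories, one gap.** A follow-up difference of 0.215 arises with nothing lost and half the controls catching up: (0.43 − 0) − 0.5 × 0.43 = 0.215. It arises equally with half the benefit lost and no control uptake: (0.43 − 0.215) − 0 = 0.215. The group difference alone cannot tell these apart.

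**6. What a persisting gap would show.** Rearranged, d − δ = D + p·b. If the programme does controls no harm on average (b ≥ 0), the maintained effect is at least D. The distortion therefore runs one way: it hides maintenance and does not create it.

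**The case against.** **The analysis is exploratory and the main comparison is clean.** This stands. The directional hypotheses run from pre- to post-intervention, the sample size rests on two time points, and controls wait until the second assessment is done. It limits the weight of the point but does not remove it, because the stated follow-up analysis still does not match its question.

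**A reader might infer that lasting benefit is bound to look like a vanished effect.** The documents do not support that. Controls are permitted to take the programme, not required to, and no uptake is given. The gap closes fully only with complete uptake and equal benefit; below that it is diluted in proportion.

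**A reader might infer that the follow-up comparison is worthless, or that the group-by-time term after post-test shows control uptake alone.** Neither holds. Immediate versus delayed access is a valid randomised comparison, and a persisting difference would be informative. The group-by-time term combines any loss in the experimental arm with any gain among controls. The arm means behind it would also help: a flat experimental line with rising controls looks different from a falling experimental line with flat controls. The risk lies in reading the between-group result by itself as the answer on maintenance.

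**The effect size is borrowed.** This is fair. The Sample size section describes d as "the estimated effect size of the change in interpretation bias before and after a CBM-I intervention". That matches the construct of AST-D-II but not of DASS-21 or PHI, so the figures illustrate the mechanism and do not forecast results.

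**The detail may sit in a separate analysis plan.** A handling rule for crossover might. But the article itself commits to a group comparison at follow-up that its own schedule has changed in meaning, so the point concerns what is stated.

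**Conclusion.** The point holds in a conditional form. At 2 weeks and 3 months the planned group differences compare immediate with delayed access, not programme with waiting list. To the extent that controls take the programme and benefit, a fully maintained d = 0.43 shrinks to (1 − p) × 0.43: 0.22 at half uptake and 0 at full uptake. A narrowing or null difference cannot be read as loss of benefit, whereas a persisting one supports maintenance.

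The size rests on assumed uptake, on controls gaining the same benefit as the experimental arm, and on applying the sample-size effect at follow-up. The power figures also assume ρ = 0.5. The existence of the problem needs only that some controls take the programme and benefit. It affects an exploratory analysis and leaves the pre/post comparison intact, so it should be fixed but does not threaten the trial's main result.

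**What to change.** Change the analysis and reporting text as follows.

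1. Limit programme-versus-waiting-list inference to the pre/post comparison.
2. Assess maintenance as the change from post-test to each follow-up within the experimental arm, using the REML mixed model already named in the Analytic plan, and label the result as uncontrolled.
3. Relabel any between-group comparison at 2 weeks or 3 months as immediate versus delayed access, and state that a narrowing gap is not evidence of lost benefit.
4. Report how many controls took the programme, how far they got and when, from the platform records. The Procedure describes these records as a means of monitoring the experimental arm; that they also cover controls is an assumption to confirm.

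The Trial status section reports the study complete by December 30, 2020, so the remedy lies in analysis and reporting and needs no new data collection if the platform kept control records. The cost is that the maintenance estimate is open to time and retest effects and must be presented as such.

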## Discussion

The current study will test the efficacy of a brief online intervention to target emotional negative cognitive biases. Although traditional CBM interventions are designed to change this type of dysfunctional processing in an automatic way [17], the rationale of ‘Relearning how to think’ is to increase participants’ awareness of their interpretation biases and guide them to change these biases , in a more effortful way, by following a clinically oriented working frame (CBM-I_Clin_).

The study uses a transdiagnostic conceptualisation of the role of cognitive biases in psychopathology. Given the high comorbidity between anxiety and mood disorders [1], having intervention tools that can tap both problems could be clinically useful. Some of the video scenarios designed for the programme were based on examples proposed by previous transdiagnostic approaches [6], and the content is suitable for different common psychopathologies in which cognitive biases may play a role.

The study also addresses some of the questions that remain unanswered regarding CBM efficacy. It combines subjective (e.g., AST-D) along with objective measures (e.g., MCAT) to assess cognitive biases. The present study aimed to complement both self-report and behavioural measures to avoid potential biases of respondents. Mental imagery is also used following the proposal that it may enhance CBM-I performance [14]. Holmes et al. [45] found that mental imagery of emotional content has a beneficial impact on cognitive change. ‘Relearning how to think’ includes imagery training to potentiate vividness of the scenarios and promote interpretation change.

Furthermore, it explores innovatively whether changes in interpretation biases may be associated with concomitant changes in attention and memory. There is very scarce basic research on the interrelation between different types of biases in emotional disorders [31], and this study will offer a unique opportunity to explore whether a specific intervention designed to change the interpretation of ambiguous scenarios may also affect other domains of information processing.

Finally, there is an increasing interest in the use of online interventions and many researchers wonder if this format is also beneficial for individuals with clinical problems. The extant evidence suggests that psychological treatments delivered online can be as effective as face-to-face therapies [72, 73] and seem to overcome some of the limitations traditional therapies present [74]. For example, online sessions can be taken by the individual at any time, there is no need to wait to schedule dates, stigma is reduced, and individuals increase their self-efficacy [75]. Specifically, CBM interventions seem to be highly suitable for the online format due to its flexibility in application, or the minimal requirement of supervision, in comparison to traditional therapies. CBM could even be used in a self-management way so that it could be applied to patients waiting for treatment or presenting vulnerability factors [28]. In sum, we expect that this study will offer new responses to some of the challenges CBM procedures face to make them more feasible, efficient, and more capable of providing answers to some theoretical issues related to the complex relations between emotion, cognition, and clinical psychology.

## Trial status

The trial was registered on June 17, 2019, with ClinicalTrials.gov NCT03987477. The study started recruiting participants on September 30, 2019, and was completed by December 30, 2020.

https://clinicaltrials.gov/ct2/show/NCT03987477?term=[name]+and+[name]&draw=2&rank=1

## Data Availability

Not applicable.

## Abbreviations

ABM: Attentional Bias Modification
AST-D-II: Ambiguous Scenarios Test for Depression-II
CBM: Cognitive Bias Modification
CBM-I: Cognitive Bias Modification of Interpretations
CBM-I_Clin_: Cognitive Bias Modification of Interpretations based on clinical procedures
CEQ: Credibility and Expectancy Questionnaire
DAS: Dysfunctional Attitudes Scale
DASS-21: Depression, Anxiety and Stress Scale-21
ECAT: Eye-gaze Contingent Attention Training
EVEA: Scale for mood
GAD-7: Generalised Anxiety Disorder Scale-7
ITT: Intention-to-treat
JTC: Jumping to conclusions
MANOVA: Multivariate analysis of variance
MAR: Missing At Random
MCAT: Mouse-based (gaze) Contingent Attention Task
PHI: Pemberton Happiness Index
PHQ-9: Patient Health Questionnaire-9
REML: Restricted Maximum Likelihood
RRS: Ruminative Responses Scale
SE: Stressful Events Questionnaire
SST: Scrambled Sentence Test
WAI-I: The Working Alliance Inventory for Internet interventions
